## Abstract

**Background:**

In malaria endemic areas, schoolchildren usually have asymptomatic malaria infections and consequently remain untreated. Therefore, intermittent preventive treatment with sulfadoxine-pyrimethamine in schoolchildren would be a plausible strategy in malaria stable transmission areas to prevent anaemia and malnutrition. However, in contrast to infancy and pregnancy, antimalaria intermittent preventive treatment in children has been barely investigated. As the implementation of intermittent preventive treatment may be challenged by sulfadoxine-pyrimethamine resistance, sulfadoxine-pyrimethamine combined with piperaquine may be a better alternative than sulfadoxine-pyrimethamine monotherapy. A clinical trial is being conducted to assess the efficacy and safety of intermittent preventive treatments versus controls in Democratic Republic of Congo (DRCongo) schoolchildren and their impact on sulfadoxine-pyrimethamine resistance.

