Favourable drugs for use as IPT should balance long half-life against efficacy, safety, tolerability and potentiality for cross-resistance selection [16]. Use of long-acting drugs would result in fewer intakes and higher treatment compliance. SP is an established product in the treatment of IPTp. The drug has further proven safety and tolerability in children in clinical trials. SP is slowly eliminated and provides 60-day antimalaria protection for fully sensitive *P. falciparum*.

Other long-acting drugs available are mefloquine, amodiaquine, and piperaquine. However, due to safety concerns, mefloquine might not be optimal for IPT. Amodiaquine is not suitable for IPT due to its three-day treatment regimen and is used as a first line treatment in several countries including DRCongo. Piperaquine has been extensively used for mass prophylaxis and treatment since 1978 in China and other malaria endemic countries of Asia [19]. Piperaquine has a long half-live and may be a good IPT candidate in malaria endemic countries [20].

Pyrimethamine binds to dihydrofolate reductase (DHFR) enzyme and sulfadoxine to dihydropteroate synthase (DHPS) and, thereby, the two SP components inhibit the *P. falciparum* life cycle [21]. However, SP resistance has spread globally due to *pf*DHFR and *pf*DHPS gene mutations as a consequence of an increasing proportion of individuals unnecessarily exposed to drugs [22]. Of note, antimalarials with lengthy elimination half-lives have a higher propensity of selecting for resistance due to exposure of new infecting malaria parasites to the drug when its concentration tail falls below the MIC [23].

To minimise the risk of SP resistance, SP could be combined with piperaquine (SP-PQ) as recommended by Cairns *et al.* and Gready [20,24]. Also, SP and SP-PQ, given at four-month intervals in line with the long half-lives (around 20 days) in paediatric patients, may improve treatment compliance. Nevertheless, evidence about the efficacy and safety of IPT SP and SP-PQ in the presence of SP resistance strains selection is not yet substantiated in schoolchildren. Only three clinical trials with restricted treatment arms and/or follow-up have so far been performed on IPTsc in hyper endemic areas. Further clinical trials are warranted in other settings. Through a randomised controlled trial (RCT) we will assess the efficacy and safety of IPT SP or SP-PQ regimens versus controls in schoolchildren of the DRCongo.

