### Study hypothesis

Considering the facts that in our study area: (1) IPT of malaria provides substantial protection against anaemia and malaria in school children; (2) the level of SP resistance has no significant impact on the prophylactic efficacy [25]; and (3) SP-PQ is safe and as efficacious as SP, we hypothesize that antimalarial IPT with SP and SP-PQ will improve haemoglobin concentration, reduce anaemia prevalence, malaria incidence and parasitaemia, and improve nutritional status and school performance in school-aged children of DRCongo.

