#### *Secondary objectives*

Secondarily, in the same study population, the purpose of the study is to:

1. Determine the prevalence of SP resistance markers at baseline and at month 12 follow-up;.

2. Compare the efficacy and safety of SP versus SP-PQ.

3. Assess the impact of antimalarial IPTsc on malaria incidence and severity.

4. Evaluate the impact of IPTsc on the nutritional status of schoolchildren.

5. Evaluate the effect of antimalarial IPTsc on school performance.

6. Identify the potential environmental and host-related predictors of malaria (re)infections.

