A previous study estimated the mean Hb concentration of 13.01 g/dl respectively in schoolchildren with IPT and 12.45 g/dl without [27]. The sample size of the study is all schoolchildren of two schools selected within the nearest schools to the regional hospital centre. The overall number of schoolchildren in the two schools is estimated to be 1,300 (650 in each school). By excluding 200 children of the sixth primary school year (100 per school), and accounting for 20% cancelation and 30% to 40% absenteeism, a realistic sample size of 616 individuals is reached for the complete IPT treatment schedule. Using this effect size and sample size, power estimates were performed by Monte Carlo simulation. In each run, a dataset was simulated assuming the within-subject variance and between-subject variability was 16, and putting in effect size to 1. The power was then estimated by fitting a linear mixed model to the data (Hb level versus treatment, time and time:treatment interaction) and testing the significance of the interaction term. The power is then equal to the fraction of times the interaction term was significant, using a significance level of 5%. A sample size of 616 offers 100% power to detect superiority between the control and the intervention groups. For the non-inferiority of SP versus SP-PQ, this sample size has over 91% power to detect a difference in effect less than 0.27 g/dl (<50%).

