### Statistical analysis plan

The effect of the type of intervention (either IPT versus the controls, or SP versus SP-P) will all be analysed using linear mixed model analysis. In each analysis, Hb concentration is modeled versus time, testing whether the change of Hb concentration over time differs between the two types of intervention. In each case, a linear mixed model is fitted with Hb concentration as outcome variable, and fixed effects including the type of intervention (indicator variable), time and the interaction between them. In these models, the effect of interest is the interaction between intervention and time, which formally tests the null hypothesis that the change in Hb concentration with time is the same in all interventions. Significance of the interaction term is tested using the F-test with a Kenwardroger correction for the number of degrees of freedom. As the study includes several (longitudinal) measurements within the same individual, and since the individuals cluster within schools, the dependency between individuals will be accounted for by including random effect terms into the model. More particularly, the model will include random effects (intercept and slope) for individual, nested within the random effect of school. An additional advantage of this technique is that it gives unbiased results in case individuals are lost to follow-up during the study.

Analysis of the data will be performed using the nlme package from the statistical software R or the proc mixed procedure from the software package SAS. All statistical analyses will be performed in close collaboration with StatUa, the Center for Statistics at the University of Antwerp.

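### The SP versus SP-PQ non-inferiority claim does not consistently fix the tested arm, the reference arm or the confidence limit that decides

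*Protocol article*

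**What the plan says.** All references are to the protocol article.

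- **Design and sample size calculation:** "For the non-inferiority of SP versus SP-PQ, this sample size has over 91% power to detect a difference in effect less than 0.27 g/dl". The figure is glossed as less than half of the 0.56 g/dl effect assumed for IPT against control. The section gives a 5% significance level for the interaction test.
- **Abstract, Background:** "sulfadoxine-pyrimethamine combined with piperaquine may be a better alternative than sulfadoxine-pyrimethamine monotherapy".
- **Abstract, Discussion:** the trial's distinctive feature is said to be the comparison of a combination therapy with monotherapy or control.
- **Background:** SP is called an established product for IPT in pregnancy, and then "To minimise the risk of SP resistance, SP could be combined with piperaquine (SP-PQ").
- **Secondary objectives:** "Compare the efficacy and safety of SP versus SP-PQ", with no direction and no mention of non-inferiority.
- **Statistical analysis plan:** the SP and SP-PQ arms are compared through the intervention-by-time interaction, "which formally tests the null hypothesis that the change in Hb concentration with time is the same in all interventions". An F-test is used, with no margin and no direction.

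**The concern.** A non-inferiority claim is one-sided. It needs a tested arm, a reference arm and a signed margin, because these decide which end of the confidence interval is read. The power sentence names SP first, so SP would have to be shown not worse than SP-PQ by 0.27 g/dl. The same sentence then describes the target as a difference below 0.27 g/dl without a sign, which reads more like equivalence. The rationale runs the other way: SP-PQ is the addition, to be judged against SP. The analysis section does not settle the matter, since a test of equality uses neither a margin nor a direction. A non-significant F-test would not establish non-inferiority of either arm, and replacing it with a confidence limit would still leave open which limit counts.

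At stake is what the trial may say about piperaquine plus SP against SP alone on haemoglobin. The trial is unblinded, so the direction should not be left to be settled after results are known.

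**Working it through.** **Inputs.** From Design and sample size calculation: margin 0.27 g/dl, power over 91%, N = 616, three equal arms, and a variance of 16 without units. Assumption: the 91% applies at zero true difference and one-sided 2.5%; the one-sided 5% reading is also shown.

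**1. The plan's own figures.**
- N: (1,300 − 200) × 0.8 × 0.7 = 616, which reproduces and gives about 205 per arm.
- Power: Φ(0.27 / (SD × √(2/205)) − 1.96). Reading 16 as a variance in (g/dl)² (SD 4 g/dl) gives 10%. Reading it as an SD of 16 g/L (1.6 g/dl) gives 40%. Reading it as a variance in (g/L)² (SD 0.4 g/dl, or 0.566 for a change) gives 99.8% to 100%, which meets over 91% only as a loose lower bound. Across all variants tried, including slope models, power ran from 7% to 100% and none came within two points of 91%. The figure is not reproduced.

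**2. Standard error implied by the stated 91%.**
- One-sided 2.5%: 0.27 / (1.960 + 1.341) = 0.082 g/dl.
- One-sided 5%: 0.27 / (1.645 + 1.341) = 0.090 g/dl.

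**3. Where the two directions part.** Let d be the observed SP-PQ minus SP difference in haemoglobin change.
- SP is non-inferior to SP-PQ if d + 1.96 × 0.082 < 0.27, that is d < 0.27 − 0.16 = 0.11.
- SP-PQ is non-inferior to SP if d − 1.96 × 0.082 > −0.27, that is d > −0.11.

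Both hold for d between about −0.11 and +0.11; outside that range exactly one holds. At d = +0.20 the 95% interval is 0.04 to 0.36: SP-PQ is non-inferior and SP is not shown to be. At d = −0.20 (−0.36 to −0.04) the verdicts swap.

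**4. Chance of each claim**, with true difference δ = SP-PQ minus SP: Φ((0.27 − δ)/0.0818 − 1.96) for SP and Φ((0.27 + δ)/0.0818 − 1.96) for SP-PQ.

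| δ (g/dl) | SP non-inferior | SP-PQ non-inferior |
|---|---|---|
| 0 | 91% | 91% |
| 0.10 | 55% | 99.5% |
| 0.135 | 38% | over 99% |
| 0.20 | 13% | about 100% |
| 0.27 | 2.5% | about 100% |

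Power at δ = 0 is the same both ways, so the stated 91% cannot reveal which direction was meant. Read as equivalence, it becomes 2 × 0.91 − 1 = 82%.

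**5. What the planned F-test can do.** At δ = 0.27 a two-sided 5% test has power Φ(0.27/0.0818 − 1.96) = 91%.

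**6. Sensitivity.**
- Over 91% is a lower bound on power, so under the one-sided 2.5% reading the standard error is at most 0.082 and the parting point lies between 0.11 and 0.27 g/dl.
- With SD 1.6 g/dl the standard error is 1.6 × √(2/205) = 0.158 and the half-width 0.31. Neither claim is met for differences within about 0.04 of zero, and exactly one is met beyond that.
- If the 91% was computed at one-sided 5%, power at one-sided 2.5% is Φ(0.27/0.0904 − 1.96) = 85%.

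**The case against.** The case for treating this as wording alone is substantial.

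- **SP versus SP-PQ may be only a label order.** The objectives and analysis sections use the same order with no direction, and the preceding power sentence lists control before intervention although the interventions are plainly the candidates. This stands as an explanation. It does not repair the sentence, which attaches the order to non-inferiority and leaves the difference unsigned.
- **The study hypothesis does not set up the opposite test.** A reader might infer a contradiction from "SP-PQ is safe and as efficacious as SP", but that phrase is in a list of facts taken as given. The hypothesis that follows concerns both IPT regimens and contains no contrast between them. The opposing orientation comes from the abstract and the Background, which discuss the rationale and do not define a formal test.
- **A reader might infer that the same data give opposite conclusions.** They do not: SP not shown non-inferior and SP-PQ non-inferior are compatible answers to different questions, and both are right if SP-PQ is better.
- **A reader might infer that the trial could not detect a benefit of piperaquine.** Step 5 shows that the F-test could, under the same assumed standard error.
- **Late choice of direction does not by itself inflate false non-inferiority claims**, since the two margin nulls cannot both be true. This also stands; the harm is an unfixed claim.
- **Sidedness of alpha and similar detail may be left to a separate analysis plan.** Agreed; silence on sidedness alone would not be a finding. Here, however, the article chose a non-inferiority claim, a margin, a power and a test, and these do not fit together.

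**Conclusion.** The point holds in limited form. The article powers a non-inferiority claim whose literal direction (SP tested against SP-PQ) differs from the orientation of its rationale. It expresses the target without a sign and analyses the pair with a test that cannot deliver a non-inferiority conclusion in either direction.

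The practical size is that the two directions give different verdicts when the observed difference exceeds about 0.11 g/dl, and agree nearer zero. That threshold rests on a standard error of about 0.082 g/dl, taken from a stated power that does not reproduce, so the probabilities are illustrations. The inconsistency itself does not depend on them. Only a secondary comparison is affected; IPT against control is untouched.

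**What to change.** In the sample-size and Statistical analysis plan sections, define one contrast, D = month-12 haemoglobin change in SP-PQ minus that in SP, with a two-sided 95% confidence interval. State in advance:

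- SP-PQ is non-inferior to SP if the lower limit is above −0.27 g/dl, and superior if the lower limit is above 0.
- SP is called non-inferior to SP-PQ only if the upper limit is below +0.27 g/dl.

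No alpha adjustment among these claims is needed. The two lower-limit nulls (D ≤ −0.27 and D ≤ 0) are nested, and neither can be true together with D ≥ 0.27.

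Restate the power sentence with the named direction and one-sided 2.5%, and delete the unsigned wording. The cost is text only, with no new data or participants. The downside is that the stated 91% may become about 85% if it was computed at one-sided 5%.

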### Study procedures

#### *Baseline, enrolment and treatment allocation*

General information on each school regarding composition, water sources, sanitation, health services, and current and previous treatments are collected by questionnaire. The social, economic and demographic patterns are recorded, physical/clinical and complementary examinations are performed, and study treatments and possible co-medications are given according to the study treatment allocation and the participant’s health status (see Table 1).

**Table 1 T1:** Follow-up chart of study participants

**Timeline in months**	**Baseline**	**4**	**8**	**12**
Informed consent	X			
Socio-economic and demographic	X			X
History (symptoms)	X	X	X	X
Examination (clinical)	X			X
Temperature	X	X	X	X
School achievement	X			X
Blood film	X	X	X	X
Hemoglobin (hemocontrol)	X	X	X	X
Thin and thick smear	X	X	X	X
Plasma sample	X			X
Filter paper PCR	X			X
Stool and urine sample	X			X
Malaria treatment^b^	X	X	X	X
Anthelminthic treatment	X	X^a^	X^a^	X
Adverse events	X	X	X	X
Concomitant medications	X	X	X	X

^a^only albendazole is given to participants. ^b^all participants will receive SP at Month 12 irrespective of the treatment allocation. In lines: we have the timelines (in months) that are displayed as baseline, month 4, month 8 and month 12. In columns are the study tasks that are performed and the parameters that are collected. X means perform this task. Blank cells mean that the specific activity will not be performed at the corresponding timeline.

#### *Follow-up visits at month 4, 8, 12*

Each study participant is followed up for 12 months. If, during the follow up, a child experiences clinical malaria or other illnesses, s/he is advised to attend the health centre for a treatment according to the national guidelines. Children absent from school at the time of the follow-up visit are seen on another day of the week for treatment and collection of three blood drops for hemocontrol and microscopy. To minimize reporting and/or recall bias, teachers in each class are encouraged to contact the site investigator when a study participant is absent or is sick (by mobile phone). Any child with a health problem is advised to consult doctors at the regional hospital of Biyela that is the health centre chosen for the study. Parents and guardians are advised to visit the health centre immediately when a child is unwell at home.

Clinical malaria cases observed during school visits are documented and referred to the Biyela regional hospital. At the end of follow-up all participants will receive one dose of SP, albendazole and praziquantel and will be passively monitored for three months [See Additional file 2].

#### *Health centre visit*

A child attending the health centre is examined and treated in line with national guidelines. All relevant medical records (history, physical and clinical examination, laboratory results, the diagnosis and the prognosis made by the clinician and the treatment given) of the patient are recorded on the CRF [see Additional file 3].

## Study drugs

### Investigational products

#### *Sulfadoxine–Pyrimethamine (SP)*

Sulfadoxine–Pyrimethamine is an established drug used for uncomplicated malaria in children and adults and for IPT in pregnant women. The safety and efficacy of SP has been widely established in infants and children in clinical trials. For the current study the Fansidar brand of SP is used. Fansidar is supplied as scored tablets, containing 500 mg sulfadoxine and 25 mg pyrimethamine unit doses. Sulfadoxine and pyrimethamine are folic acid antagonists. Sulfadoxine inhibits the activity of dihydropteroate synthase whereas pyrimethamine inhibits dihydrofolate reductase. *In vitro*, sulfadoxine and pyrimethamine are active against the asexual erythrocytic stages of *P. falciparum*. SP may also be effective against strains of *P. falciparum* resistant to chloroquine. Fansidar is approved and commercialised for the treatment of uncomplicated malaria and the prevention of malaria.

Owing to its slow elimination profile, levels of SP sufficient to inhibit parasite growth persist for 60 days after treatment, providing a period of post-treatment prophylaxis during which successful development of a blood-stage infection is prevented. After administration of one tablet, peak plasma levels for pyrimethamine (approximately 0.2 mg/L) and for sulfadoxine (approximately 60 mg/L) are reached after about four hours. The volume of distribution for sulfadoxine and pyrimethamine is 0.14 L/kg and 2.3 L/kg, respectively. Plasma protein binding is about 90% for both pyrimethamine and sulfadoxine. A relatively long elimination half-life is characteristic of both components. The mean values for plasma elimination half-lives are up to 11 days for sulfadoxine and 5 days for pyrimethamine, mainly via the kidneys [28].

Fansidar is given as a single oral dose of ½ tablet of 500 mg sulfadoxine - 25 mg pyrimethamine per 10 kg of weigh: 1 tablet for weight less than 20 kg, 1.5 tablets for 20 to 29 kg, and 2 tablets for children who weigh 30 kg or more.

#### *Piperaquine*

PQ is not approved as a single entity. A fixed dose combination of PQ with dihydroartemisinin (DHA) was approved by the European Medicines Agency and marketed as Eurartesim for the treatment of uncomplicated malaria in children and infants of six months or older. The exact mechanism of action of PQ is unknown. PQ likely mirrors its closest structural analogue chloroquine. Chloroquine binds to toxic haeme (derived from the patient’s haemoglobin) within the parasite and prevents its detoxification. The Cmax and the AUC0-24 of PQ is 179 nm/ml and 1.679 ng/ml*h, respectively. The elimination half-life of PQ is around 20 days for paediatric patients. Due to its slow elimination, PQ may accumulate in plasma after multiple doses. In healthy volunteers, PQ exposure is increased approximately three-fold when administered with a high fat/high calorie meal. In combination curative treatment with DHA, PQ is safe and efficacious at 60 to 73.9 mg/kg dose in three daily doses against uncomplicated *P. falciparum* malaria [29,30]. However, because participants in this trial are healthy individuals, the parasite carriage is expected to be low. Taking account of the ED90 of PQ at 1.68 ± 0.210 mg/kg/day for *P. berghei* K-173, its CT100 of 42 hours and the long elimination half-life [31], PQ 320 mg tablets manufactured by Sigma Tau will be used at two treatment doses of 16 to 24 mg/kg body weight at 24-hour intervals (in combination with SP) as follows: 1 tablet for weigh 15 to 19 kg, 1.5 tablets for 20 to 29 kg, 2 tablets for 30 to 39 kg, and 2.5 tablets for 40 kg or more. The treatment will be administered with water under fasting conditions.

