### Patient selection and withdrawal

#### *Inclusion criteria for initial treatment*

In order to be eligible, children should satisfy all of the following criteria:

1. Male and female primary school children.

2. Anticipated local residence for the study duration.

3. Signed or thumb-printed informed consent by the parents or guardians and witnessed by an impartial witness (whenever parents/guardians are illiterate).

4. Informed consent for children 12-years-old or older.

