#### *Exclusion criteria*

Participants with at least one of the following criteria are excluded:

1. Children of the sixth primary school year.

2. Participation in any other investigational drug study (antimalarial or others) during the previous 30 days.

3. Known or suspected hypersensitivity or serious adverse events (AE) to the study drugs.

4. Malaria symptoms at baseline irrespective of the severity [see Additional file 1].

5. Febrile conditions caused by diseases other than malaria at the first visit.

6. Decompensated anaemia.

7. Illness or conditions, such as hematologic, cardiac, renal, hepatic diseases, which in the judgement of the investigators would place the subject at undue risk or interfere with the results of the study, including known glucose-6-phosphate dehydrogenase deficiency and sickle cell.

8. Body weight <14 kg.

9. Children with major chronic infectious diseases (HIV, tuberculosis, and so on).

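### Eligible children of 14 to under 15 kg allocated to SP-PQ have no defined piperaquine dose, and the open top weight bands fall below the stated per-weight doses above 50 kg (piperaquine) and 40 kg (SP)

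*Protocol article*

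**What the plan says.** All references are to the protocol article.

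- **Exclusion criteria, item 8:** the only weight limit is "Body weight <14 kg". A child of 14.0 kg or more passes it.
- **Inclusion criteria:** entry is open to "Male and female primary school children", and no upper weight limit appears in either list. Sixth-year pupils are excluded.
- **Piperaquine:** "PQ 320 mg tablets manufactured by Sigma Tau will be used at two treatment doses of 16 to 24 mg/kg body weight at 24-hour intervals". The bands that follow are "1 tablet for weigh 15 to 19 kg, 1.5 tablets for 20 to 29 kg", then "2 tablets for 30 to 39 kg, and 2.5 tablets for 40 kg or more". Nothing is printed below 15 kg, and the last band has no upper end.
- **Sulfadoxine–Pyrimethamine (SP):** the dose is half a tablet for each 10 kg, followed by three bands. These are 1 tablet under 20 kg, 1.5 tablets from 20 to 29 kg, and "2 tablets for children who weigh 30 kg or more".
- **Randomisation and treatment allocation:** children are allocated 1:1:1 in blocks within school, with no condition on weight.

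**The concern.** The eligibility limit and the piperaquine table should meet at the same weight, and they miss by 1 kg. Allocation takes no account of weight, so a child in that interval can be drawn into SP-PQ. The person giving the drug would then have no protocol dose to follow. The section on treatment administration requires study drug to be used only as the protocol sets out, so staff have no stated authority to fill the gap. The piperaquine section also notes that the drug has no approval on its own and may accumulate with repeated doses. That is reason enough not to leave the dose of the lightest eligible children undefined.

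The top bands raise a lesser question. A fixed number of tablets with no upper weight limit must at some weight drop below any stated per-kilogram figure. The article gives both, so the two can be compared.

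**Working it through.** **Inputs.** Eligible from 14 kg, with no upper limit (inclusion and exclusion criteria). Piperaquine tablet 320 mg, stated range 16 to 24 mg/kg, four bands (piperaquine section). SP rule of half a tablet per 10 kg, three bands (SP section). Band labels are read as completed kilograms, so that the first piperaquine band runs from 15.0 to just under 20 kg.

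**1. Lower end, side by side.**

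| Weight | Eligible? | SP band | Piperaquine band |
|---|---|---|---|
| under 14 kg | no | not needed | not needed |
| 14 to under 15 kg | yes | 1 tablet | none |
| 15 to under 20 kg | yes | 1 tablet | 1 tablet |

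Rounding does not close the gap. With completed kilograms the whole interval from 14 to under 15 kg is uncovered. With rounding to the nearest kilogram, 14.0 to under 14.5 kg is still uncovered.

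**2. Does the piperaquine table reproduce the stated range?** Dose per kg = tablets × 320 / weight.

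| Band | Dose | At lower edge | At or near upper edge |
|---|---|---|---|
| 15–19 kg | 320 mg | 320/15 = 21.3 | 320/19.99 = 16.0 |
| 20–29 kg | 480 mg | 480/20 = 24.0 | 480/29.99 = 16.0 |
| 30–39 kg | 640 mg | 640/30 = 21.3 | 640/39.99 = 16.0 |
| 40 kg and over | 800 mg | 800/40 = 20.0 | 800/50 = 16.0 at 50 kg |

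From 15 to 50 kg the table returns 16 to 24 mg/kg exactly. This also settles that the range applies to each of the two doses: as a total over both doses, the same weights would give 32 to 48 mg/kg.

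Beyond 50 kg: 800/51 = 15.7, 800/55 = 14.5, 800/60 = 13.3 mg/kg. The crossing point is 800/16 = 50 kg.

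**3. SP top band against the SP rule.** Half a tablet per 10 kg, taken as a straight proportion, is weight/20 tablets.

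| Weight | Rule (tablets) | Band (tablets) | Band / rule |
|---|---|---|---|
| 30 kg | 1.5 | 2 | 1.33 |
| 40 kg | 2.0 | 2 | 1.00 |
| 45 kg | 2.25 | 2 | 0.89 |
| 50 kg | 2.5 | 2 | 0.80 |

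The band drops below the rule above 40 kg. If the rule is instead read as half a tablet for each 10 kg begun, it gives 1, 1.5 and 2 tablets in the tens, twenties and thirties, which are the printed bands. From 40 kg it would give 2.5 tablets against the printed 2. The top-band mismatch appears on both readings.

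**4. Scale.** The article gives no weight distribution. Its sample-size section implies 1,300 − 200 = 1,100 children, 1,100 × 0.8 = 880 after 20% cancellation, and 880 × 0.7 = 616 after 30% absenteeism. That is 616/3 ≈ 205 to 880/3 ≈ 293 per arm. Each 1% of the SP-PQ arm is thus about 2 to 3 children. If the share weighing 14 to under 15 kg were anywhere from 0 to 3% (an assumption with no source in the article), 0 to about 9 SP-PQ children would be concerned (0.03 × 293 = 8.8).

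**The case against.** Several points can fairly be made on the other side.

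- *This is a condensed article.* A fuller dosing table may exist, and the section on treatment administration refers to each product's brochure, which is not shown. That may soften the practical risk. It does not remove the mismatch, because the article prints both the eligibility limit and the bands, and they disagree.
- *The SP bands are not in conflict with their rule.* A reader might infer that SP is given at up to 1.5 times the stated dose, since 20 kg would call for 1 tablet against a printed 1.5 (and 14 kg for 0.7 against 1). The article does not support that inference. The bands follow the rule after a colon and can be read as its application per 10 kg begun, which reproduces all the bands below 40 kg. This objection stands, and only the part from about 40 kg upward remains.
- *SP has a printed dose at every weight, and piperaquine has one at every weight from 15 kg.* This is correct. Only the interval from 14 to under 15 kg in SP-PQ is undefined. At the top, the dose is printed but disagrees with the per-weight figure beside it.
- *Heavy children may not exist here.* More than 50 kg would be unusual in primary school with the sixth year left out, and the article does not show that any such child enrols. This is fair. The table does, however, provide a separate piperaquine band from 40 kg, so children at the SP cut-off are foreseen.
- *The trial comparison is harmed.* A reader might infer that missing piperaquine doses, which can arise in one arm only, blur SP versus SP-PQ. No figure in the article supports a material effect: the share of children is unknown, and the SP bands are common to both active arms.

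**Conclusion.** The contradiction at the lower end is real: a child of 14 to under 15 kg is eligible, can be allocated to SP-PQ and has no piperaquine dose in the article. It concerns one drug, one arm and a 1 kg interval (half a kilogram if weights are rounded to the nearest kilogram).

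The top bands are secondary points with exact cut-offs. Piperaquine falls under its own 16 mg/kg above 50 kg. SP falls under its own rule above 40 kg on the proportional reading, or from 40 kg on the per-started-10-kg reading. Below those weights the piperaquine bands from 15 kg match the stated range, and the SP bands can be squared with their rule.

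The number of children affected is unknown and may be small or nil. Power is unaffected, and no bias in any treatment comparison has been shown. The reason to act is that every enrolled child should have a defined dose, and the trial status section says that recruitment is under way.

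**What to change.** Reconcile three places in the article and in the working protocol: item 8 of the exclusion criteria, the piperaquine bands with their mg/kg range, and the SP rule with its top band. After the change, every eligible child in SP-PQ should have one defined piperaquine dose, and the open top bands should agree with the per-weight figures stated beside them. The text should also say how weights are rounded when a band is chosen. Whether the eligibility limit, a band or a stated range changes is for the sponsor's clinicians.

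Because the trial is recruiting, the clarification should go out promptly. It would help to check whether any child of 14 to under 15 kg has already been allocated to SP-PQ, and to record what was given. The cost is a short protocol clarification and an updated dosing card. The sample size and analysis do not change.
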